**Aims of the Study:**

***Describe the aims/objectives of the research and/or the project’s research questions or hypotheses.***

The Bloomberg Philanthropies Data for Health initiative aims to strengthen the collection and use of critical public health information. One of the components of the initiative seeks to explore innovative approaches to non-communicable disease (NCD) surveillance, including the use of mobile phone surveys for NCDs, in 10 countries. The main objectives of the component are to assess the feasibility, quality, and validity of NCD mobile phone surveys.

This protocol builds onto currently approved protocols for the *formative phase* (JHU IRB No: 0000709); where the aim of the formative phase is to contextualize the use of mobile phone surveys on an *Interactive Voice Response* (IVR) platform for usability and optimal performance in participating countries. This IRB submission describes the **optimization phase** of the NCD risk factor mobile phone survey.

This protocol’s overall goal is to answer key questions on how to improve IVR survey participation and how mobile phone survey modalities (IVR versus Computer Assisted Telephone Interview [CATI]) differ on key survey performance metrics. With IVR surveys, respondents interact with a pre-programmed database which contains both questions, and a series of pre-set answers to the questions - linked to a specific numeric key, or numeric response on a touch-tone phone keypad (e.g. “Press 1 for Yes”). CATI surveys employ call centers where human interviewers follow a script provided by a software program to survey participants. These results will inform future implementation of mobile phone surveys in low- and middle-income countries (LMICs). Through a set of seven rapid, “*microtrials”*, the protocol seeks to:

Primary Objectives:

1. Evaluate the impact of *incentives* on response, completion, and refusal rates of an IVR-administered NCD risk factor survey.
2. Assess the effect of different IVR survey *introduction modalities* on response, completion, and refusal rates of an IVR-administered NCD risk factor survey.
3. Examine the differences in survey metrics, such as representativeness, completeness, and response rate, between random digit dialing (RDD) approaches and existing sources e.g., Mobile Network Operators (MNO).
4. Evaluate the differences in survey metrics between an IVR Survey and a Computer Assisted Telephone Interview (CATI).

**II. Background and Rationale:**

***Explain why this study is being done. Summarize briefly what is already known about the issue and reference previously published research, if relevant.***

Non communicable diseases (NCDs) are a growing burden in lower- and middle-income countries (LMICs).^1-3^ Approximately 28 million, or 75%, of all NCD deaths occur in lower and middle income countries.^4^ Physical inactivity, poor diet, alcohol use, and smoking are the four most common risk factors associated with NCDs.^5^

To assess the burden and prevalence of NCDs and risk factors, the World Health Organization (WHO) supports countries with the implementation and analysis of the STEPS survey.^6^ The STEPS survey contains three steps, or components, of NCD surveillance: (1) self-reported risk factor questionnaire, (2) physical measurement, and (3) biochemical measurement. The risk factor questionnaire contains questions on tobacco use, alcohol consumption, diet, physical activity, history of NCDs, and lifestyle advice and it is administered face-to-face (F2F) with the respondent. The remaining two steps do not employ questionnaires, but rather take physical measurements (such as height and weight) and biochemical measurements (blood glucose).

Although the World Health Organization supports a household survey (STEPS) to assess national level NCD risk factor prevalence, the high costs and time commitments of conducting such face-to-face surveys means that they are only conducted approximately every 5-10 years. A more frequent collection of NCD risk factors could address gaps in NCD surveillance, assist policy makers by directing resources to NCD prevention programs, and also allow for a more timely assessment of such policies and programs, while also complementing existing data sources with additional population-level insights.

To address the high costs and time requirements associated with household surveys, higher income countries have developed and employed telephone and mobile phone surveys to collect population-level estimates of health and demographics.^7-9^ Concomitant with the global increase in mobile phone ownership and access^10^ opportunities exist to leverage mobile-health technologies and communication channels to revolutionize the current methods of data collection in low- and middle-income countries (LMIC)--- face-to-face interviews at respondent’s household--- by now interviewing respondents over their own personal mobile phone through the use of short message service (SMS; or ‘text message’), interactive voice response (IVR), and computer assisted telephone interviews (CATI) survey modalities; collectively called mobile phone surveys (MPS). This protocol focuses on mechanisms to optimize the performance of IVR surveys conducted in LMICs and to compare how different survey modalities (i.e. CATI versus IVR) affect the survey metrics.

As MPS in LMIC settings are relatively new, there is a dearth of scientific evidence on factors that affect MPS’s response, completion, and attrition rates and corresponding mechanisms to improve them in this context. The optimization of surveys with respect to incentives, survey introductions, and sampling frame (i.e. source of mobile phone number) to improve these survey metrics strengthens scientific rigor and the rationale for future nationally administered MPS, and has the potential to create significant cost-savings by enhancing survey response and completion rates.

**III. Study Design**

A. ***Provide an overview of your study design and methods. The study design must relate to your stated aims/objectives. Details will be requested later.***

The following objectives will be conducted in four of the following six countries: Uganda, Bangladesh, Tanzania, Kenya, Lebanon, and Ghana. The Bloomberg Philanthropies Data for Health Initiative (under which this work falls), has secured high level government agreements for Tanzania, Bangladesh, and Ghana to date. The four objectives detail a series of seven microtrials. Microtrials will be rapidly deployed, randomized survey deployments of limited sample sizes, sufficient to detect a consequential difference, as described below in Table 2 and will be sent through random digit dialing (RDD). RDD uses the mobile network operator identifying digit sequence as the base (e.g.all of MNO X’s phone numbers start with either 072, 077, or 079) and randomly generates the remaining digits to create a mobile phone number. A built-in randomization schema will randomly fork each dialed participant to one of the arms of the microtrial. To achieve these objectives, JHSPH will partner with in-country research institutes and government bodies. The countries will lead the research activities with support from JHSPH. JHSPH investigators will have no contact with research participants. VOTOmobile, a company that specializes in delivering IVR surveys globally, will be contracted to deliver the mobile phone surveys. De-identified data will be jointly shared with JHSPH and in-country partner investigators.

**Objective 1: Evaluation of the impact of incentives.** We will conduct three *microtrials* in order to assess the effect of providing airtime incentives on contact, response, completion, refusal, and attrition rates of IVR surveys. Prior to the first *microtrial*, we will conduct a baseline IVR survey to establish baseline completion rates and to finalize the questionnaire (see more details below). *Micro-trial #1* will assess whether the amount of incentive (e.g. 1 USD vs 2 USD) affects the survey metrics listed above. This incentive will be given to individuals who complete the IVR survey. *Micro-trial #2* will examine the effect of the incentive delivery’s timing (e.g. providing an incentive at the start of the survey versus at the end). The *third* micro-trial will assess the effect of the incentive structure by comparing survey metrics in those who receive a fixed incentive amount versus those who receive a ‘lottery’ incentive, where a lottery incentive is larger but only given to a small percentage of respondents. The contact, response, completion, refusal, and attrition rates will be calculated overall and stratified by key demographics.

**Objective 2: Evaluation of the impact of the survey’s introduction.** We will conduct two *microtrials* in order to assess the effect of the survey’s introduction on key survey metrics. *Micro-trial #3* will examine the introduction content (motivational vs informational) and survey’s voice (male vs female). *Micro-trial #4* will examine the effect of the introduction’s modality by observing differences in survey metrics in those who have a human operator provide the introduction, versus those who receive an IVR introduction. The contact, response, completion, refusal, and attrition rates will be calculated overall and stratified by key demographics.

**Objective 3: Evaluation of the impact of the survey’s sampling frame.**

The five *microtrials* presented in Objectives 1 and 2 will be sent to phone numbers that were randomly generated (i.e. a random digit dial [RDD] approach). Objective 3’s *microtrial* will send IVR surveys to a list of de-identified phone numbers that were provided by a mobile network operator (MNO; i.e. a cell phone company) and/or which were collected from a previous household survey where consent was collected. We will compare the demographic representativeness, response rate, completion rate, and cost from the IVR survey sent using MNO provided phone numbers with the IVR surveys from Objectives 1 and 2 in order to assess the effect of the sampling frame on these key survey metrics.

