**Objective 4: Evaluation of the impact of the survey’s modality.**

We will conduct one *microtrial* in order to assess the effect of the survey’s modality (IVR versus CATI) on key survey metrics as described above and to assess inter-modal reliability. A group of participants will receive an IVR survey first, followed by a CATI survey 7 days later. A second group of participants will receive a CATI survey first followed by an IVR survey 7 days later. Whether a participant receives IVR or CATI first will be determined at random, blocking to ensure balance between IVR and CATI participation.

*B.* ***Provide a sample size and a justification as to how you arrived at that number. If you use screening procedures to arrive at a final sample a table may be helpful.***

A description of sample size calculations is provided below in the text and is accompanied with a table.

Baseline Survey: We selected 100 participants with complete surveys as a sample size because we think this a sufficient size sample to ascertain that the survey, incentive, and text message delivery mechanisms are well functioning. Adjusting our sample size to account for a baseline completion percentage of 30% (estimate provided by VOTOmobile), we anticipate to consent and enroll 334 participants per country; 1336 participants in four countries.

Microtrial 1-6:

Sample size calculations will be updated with country-specific completion percentages obtained from the baseline survey.

Assuming a baseline survey completion percentage of 30%, in order to detect an absolute 10% difference in survey completion between two study arms at an alpha of 0.05 and power of 80%, it is calculated that 376 individuals who have completed an IVR survey will be needed in each study arm for each microtrial. With a completion percentage of 30%, we calculated that 1254 participants will be required to consent to the survey per study arm. With 16 study arms in these 6 micro trials, 20,064 participants will be enrolled per country; 80,256 participants in four countries.

Microtrial 7:

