This sample size is calculated based on the kappa statistic. With assumption of kappa= 0.75, a margin of error of 0.05%, an alpha of 0.05, and the proportion of positive responses=0.3, 405 participants who have completed the survey per study arm are needed. Adjusting for a 20% loss to follow-up from the first and second mobile phone survey and a 30% baseline completion percentage, 1688 participants who consented will be enrolled per arm and per country, for a total of 3376 participants across the two arms per country. With two arms and 4 countries, a total of 13,504 participants who provide consent across the four studies are needed.

Total Sample Size

For the baseline survey and seven microtrials, in each country, a total of 23,773 individuals who have consented to an MPS survey will be needed to fulfill a sample size of 6926 individuals who completed an MPS survey per country. As this protocol is being implemented in four countries, the overall sample size is 95,092 individuals who have consented to an MPS survey and 27,704 who completed a MPS survey

**Table 1.** Number of participants who consent to and complete a mobile phone survey per country

|  | **Col. A** | **Col. B** | **Col. C^*^**  [(Col B*100)/0.30] | **Col. D**  [Col A*Col B] | **Col. E**  [Col A*Col C] |
| --- | --- | --- | --- | --- | --- |
|  | # of study arms | N participants who completed survey per study arm | N participants who consented per study arm | Total N participants who completed survey | Total N participants who consented |
| **Objective 1** |  |  |  |  |  |
| *Baseline* | 1 | 100 | 334 | 100 | 334 |
| *Microtrial #1* | 3 | 376 | 1254 | 1128 | 3762 |
| *Microtrial #2* | 3 | 376 | 1254 | 1128 | 3762 |
| *Microtrial #3*** | 3 | 376 | 1254 | 1128 | 3762 |
| **Objective 2** |  |  |  |  |  |
| *Microtrial #4* | 4 | 376 | 1254 | 1504 | 5016 |
| *Microtrial #5* | 2 | 376 | 1254 | 752 | 2508 |
| **Objective 3** |  |  |  |  |  |
| *Microtrial #6* | 1 | 376 | 1254 | 376 | 1254 |
| **Objective 4** |  |  |  |  |  |
| *Microtrial #7* | 2 | 405 | 1688 | 810 | 3376 |
| **Total** |  |  |  | 6926 | 23,773 |

* For microtrial 7, we adjust for a 20% loss to follow-up from the first and second mobile phone survey.

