This microtrial seeks to examine whether the survey introduction’s modality (human operator versus those who receive an IVR survey introduction) has an effect on survey response and completion rates. Participants will be randomized to one of two arms: 1) a human will call the RDD-generated mobile phone number and read the survey’s introduction. The operator will answer any questions the participant may have, consent the participant and then patch the participant into the IVR survey, and 2) the participant will receive a IVR survey with a survey introduction in IVR format and similar to the previous *microtrials*.

Objective 3: Evaluation of the Sampling Frame

*Microtrial #6*- Evaluation of the sampling frame of mobile phone numbers

This microtrial seeks to examine whether the source of the mobile phone numbers has a differential effect on the IVR survey’s response and completion rates. The previous five *microtrials* relied on a RDD sampling frame. In this microtrial, we will obtain a de-identified list of mobile phone numbers from either a mobile network operator or from a previously conducted household survey where participants had consented to be contacted for additional studies. Participants will be sent an IVR survey with the top performing survey introduction (results from microtrials 4 and 5) and the top performing incentive (microtrials 1-3).

Objective 4: Evaluation of Survey Modality

*Microtrial #7*- Evaluation of CATI and IVR survey metrics

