| **Notes** | -First microtrial to be conducted  -Incentive given after completion of IVR survey (Post-IVR) | -Incentive amount will range from X to 2X | -1:20 odds of winning lottery; incentive is 5 times amount in fixed incentive arm | -Provide same incentive in each arm  -The only difference in the questionnaire is the survey’s introduction. | -Human intro is a call center that asks participants if they wants to participate and if so, patches them into an IVR  -Provide same incentive in each arm | -Incentive and survey introduction used are top performers from microtrials #1-4 | - IVR arm will receive IVR survey first, followed by CATI survey 7 days later  -- CATI arm will receive a CATI first followed by an IVR survey 7 days later. |

Abbreviations: CON, contact rate; MNO, mobile network operator; RR, response rate, COMP, completion rate; R, refusal rate

***2. Describe the number and type of study visits and/or contacts between the study team and the participant, how long they will last, and where/how they will take place.***

There will be no face-to-face (i.e. in-person) contact between participants and the study staff. All interactions with research participants will be through the participant’s personal mobile phone. Participants will be randomly selected from a list of randomly generated mobile phone numbers (microtrials 1-5) or from a pre-defined and de-identified list of mobile numbers provided by a MNO or household survey. The selected mobile phone number will be sent one text message that alerts the potential participant about the upcoming survey. For all *microtrials* except for *microtrial #7,* participants will be sent one MPS. If a participant decides to answer the MPS, the time to complete the survey should be no more than 30 minutes. For *microtrial #7*, participants will be sent a CATI and IVR survey separated by seven days. In a sub-sample of participants who either refused to participate in the IVR survey, did not initiate the survey, or who did not complete the survey, participants will be called back by a human operator to understand reasons for their not fully participating in the survey. This interview is expected to take no more than 30 minutes. Therefore, participants may have up to three contacts with the mobile phone survey. For each contact, a verbal consent will be taken.

***3. Describe the expected duration of the study from the perspective of the individual participant and duration overall.***

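### Microtrial 6 has no concurrent, package-matched RDD comparator, so Objective 3 cannot attribute a difference to the sampling frame

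*Protocol*

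**What the plan says.** Section I lists the comparison of RDD with existing number sources as a primary objective. Under Objective 3 in section III.A, the list-based survey is set against earlier surveys: "with the IVR surveys from Objectives 1 and 2 in order to assess the effect of the sampling frame on these key survey metrics". The metrics named there are demographic representativeness, response, completion and cost.

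The Microtrial #6 description in section V.C.1 fixes four things:

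- **Source of numbers:** "we will obtain a de-identified list of mobile phone numbers from either a mobile network operator or from a previously conducted household survey". No RDD sample is included.
- **Timing:** the five preceding microtrials "relied on a RDD sampling frame", and microtrial 6 follows them because it uses their results.
- **Package:** the survey goes out "with the top performing survey introduction (results from microtrials 4 and 5) and the top performing incentive (microtrials 1-3").
- **Arms:** Table 1 gives microtrial 6 one arm, with 376 completes and 1,254 consents per country.

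The Table 2 note for microtrial 6 describes the package differently: "Incentive and survey introduction used are top performers from microtrials #1-4".

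The sample size for microtrials 1 to 6 (section III.B) is meant to "detect an absolute 10% difference in survey completion between two study arms", from a baseline of 30%, with alpha 0.05 and 80% power.

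**The concern.** The RDD surveys of Objectives 1 and 2 form 15 arms. Three offer no incentive (one in each of microtrials 1, 2 and 3). Others use a lottery, a part-prepaid incentive or different amounts, and the arms of microtrials 4 and 5 use several introductions. Microtrial 6 carries the best performers from this set and runs later.

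A list-versus-RDD contrast therefore changes up to three things at once: the source of the numbers, the incentive and introduction package, and the calendar period. The programme is built on the expectation that incentives and introductions move completion by amounts worth detecting. If they do, part of that movement can be reported as an effect of the frame. Cost is affected too, because the package determines what is paid per complete. At stake is whether a primary objective can be answered as worded, and advice to countries on whether operator lists outperform RDD.

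**Working it through.** **1. The plan's own figure.** Inputs from section III.B: 30% against 40%, two-sided alpha 0.05 (sidedness is not stated; two-sided reproduces the figure), power 80%.

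n = [1.96·√(2·0.35·0.65) + 0.842·√(0.3·0.7 + 0.4·0.6)]² / 0.10² = 356 per arm; with continuity correction 376. Then 376/0.30 = 1,254 consents (rounded up). Both figures in Table 1 reproduce, so the fault lies in the design and not in the arithmetic.

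**2. Count of RDD arms.** Table 1, microtrials 1 to 5: 3 + 3 + 3 + 4 + 2 = 15, of which 3 have no incentive.

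**3. Package bias with no frame effect.** Assumption, borrowed from the plan's effect size: 30% completion in the no-incentive arms, 40% in all others and in microtrial 6, equal arm sizes.

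- Pooled RDD rate: (3×30 + 12×40)/15 = 38%. Apparent frame effect: 40 − 38 = +2 points.
- Against the no-incentive arms alone: 40 − 30 = +10 points.
- If introductions also matter, the pooled figure grows.

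**4. How often such a shift would be declared significant.** No true frame effect, comparator at 30%, two-sided 5% test, and a shift from package or calendar time of the size shown. The last two columns count consenters.

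| Shift | 376 per group | 1,254 per group | 1,254 against 15 × 1,254 |
|---|---|---|---|
| 2 points | 9% | 19% | 32% |
| 5 points | 31% | 76% | 96% |
| 10 points | 82% | >99.9% | >99.9% |

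The documents give no estimate of calendar drift, so the shifts are a range and not a forecast.

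**5. A winning arm reused as comparator.** If k arms have equal true rates of 30% and the best observed one becomes the comparator, its rate is overstated at 1,254 per arm by 0.7, 1.1 or 1.3 points for k = 2, 3 or 4. Type I error becomes about 5%, 6% or 8%. This bias works against the list frame, opposite to step 3. Equal true rates are the worst case.

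**6. The remedy's power.** Two samples of 627 consenters, 30% against 40%:

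- Null SE √(2·0.35·0.65/627) = 0.0269; alternative SE √(0.45/627) = 0.0268.
- z = (0.10 − 1.96×0.0269)/0.0268 = 1.76, so power is about 96%.

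Consenters are a fair basis: the completion rate in section V.C.4 divides by complete interviews, partial interviews and refusals, so its denominator contains at least the consenters.

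**7. The remedy's price.** Completes per sample: 627×0.30 = 188. The SE of a 50% proportion among completes rises from √(0.25/376) = 2.6 points to √(0.25/188) = 3.6 points.

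**The case against.** Several counter-arguments have force.

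- **Pooling is not stated.** A reader might infer that all 15 RDD arms will be pooled. Objective 3 does not say so, and an SAP, not shown here, could choose the comparator. An arm of microtrial 5 might come close to microtrial 6's package. This stands: package confounding is avoidable if a matched arm exists. But the protocol says only that incentives are the same across the arms within microtrials 4 and 5, not that they are the winning ones. Even a perfect match would leave calendar time mixed with frame, and no analysis can supply concurrent RDD data that were not collected. Microtrial 7 is RDD with the best incentive, but Objective 3 does not name it as comparator, and its participants are told that they will be contacted twice.
- **Winner selection is minor.** A reader might infer that the list frame must look worse against a winning arm. The documents do not support that: it depends on which arm is used and on near-equal true rates, and the bias is small beside the 10-point design effect.
- **The sample size is not wrong because there is one arm.** A list arm of 376 against an RDD arm of 376 is still a two-group contrast of the planned size.
- **Drift may be small.** The questionnaire is the same in microtrials 1 to 6, delivery is similar, and deployment is meant to be rapid. This limits the likely size but does not remove the confounding.
- **The introduction mismatch may be editorial.** Section III.A, Objective 2, numbers the introduction trials 3 and 4, so the Table 2 note may follow older numbering. A reader might infer two different plans for the human introduction; the text does not establish that.
- **Frame cannot be randomised.** True, and the remedy does not claim to. It balances time and package, which is what is missing.

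**Conclusion.** The point holds. As designed, microtrial 6 cannot attribute a difference in response, completion or cost to the sampling frame. Calendar time is confounded with frame under any choice of comparator, and the package is confounded too unless a matched RDD arm is used, which the protocol neither names nor guarantees.

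The size depends on that choice. Under the assumed 30% and 40% rates with no frame effect, the apparent advantage of the list is 2 points against pooled RDD arms and 10 points against no-incentive arms, though no text proposes the latter comparison. Reusing a winning arm gives about 1 point in the opposite direction at 1,254 per arm. Since even the sign depends on an unnamed comparator, the reported frame effect would be hard to interpret. The planned sample size is correct as arithmetic and is not part of the problem.

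**What to change.** Run microtrial 6 as two concurrent samples within the planned 1,254 consenting participants per country: about 627 from the list and about 627 from freshly generated RDD numbers. The 627 are people who consent, not numbers dialled. Mix the two sets, dial them in random order over the same days, and give both the same incentive and introduction. Use that contrast alone for Objective 3, and keep comparisons with microtrials 1 to 5 descriptive.

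**Cost.** No extra consents are needed, and RDD generation is already in place. Power for 30% against 40% completion among consenters is about 96%. Each sample yields only about 188 completes, so the plan's rule of 376 completes per arm is not met and must be waived explicitly for this microtrial. Representativeness becomes less precise (SE 3.6 instead of 2.6 points for a 50% proportion). If that is not acceptable, a full second arm costs a further 1,254 consents and 376 completes per country (microtrials 1 to 6: 17 × 1,254 = 21,318 consents instead of 20,064).

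Also reconcile the Microtrial #6 text with the Table 2 note on which microtrials supply the introduction. If the present design is kept, the protocol should call Objective 3 a descriptive comparison and drop the word effect.
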